### Participants and eligibility

2.2

Primary outcomes of this pilot study are feasibility measures (e.g., adherence, attrition, motivation, enjoyment, adverse events) which do not require an *a priori* sample size calculation. The selected sample size is based on the recommendations of Whitehead et al. (25). Since we are aiming for a future main trial designed with 90% power and two-sided 5% significance and aim to be able to detect medium effect sizes, we will use a sample size of n = 15 per treatment arm. Therefore, 30 participants will be included in the study with 15 participants allocated to each group (intervention or control group). Inclusion criteria are: prescription for inpatient rehabilitation due to a stroke, ability to provide a signed informed consent, age ≥ 50 years, Mini Mental State Examination (MMSE) ≥ 20, ability to stand for at least 3 min without external support. Exclusion criteria are: depending on assistance for ambulation (Functional Ambulation Categories <2), insufficient knowledge of the German language to understand the instructions and games, conservatively treated osteoporotic fractures in the last 16 weeks and presence of any mobility, cognitive, sensory and/or psychiatric limitations or comorbidities which impair the ability to play the exergames and/or conduct the pre-/post assessments.

### Interventions

2.3

This study will have two arms: a control group for which the conventional treatment during the stay in the inpatient rehabilitation clinic includes a cognitive-motor intervention on a stable surface using the exergame device Senso (Dividat AG, Schindellegi, Switzerland, CE certified, see Figure 1) and an intervention group where the conventional treatment during the stay in the inpatient rehabilitation clinic is extended with an exergame-based cognitive-sensorimotor intervention on an unstable surface by placing the Senso on an unstable surface (Senso-Swing, see Figure 2).

**Figure 1 fig1:**
[figure not shown]
Senso.

**Figure 2 fig2:**
[figure not shown]
Senso-Swing.

The Senso is a platform for the dynamic recording of steps, weight shifts and other body movements producing forces. The feedback for the user is given visually and auditory by the screen and tactile by vibrating plates. For the labile condition, the Senso is mounted on steel balls, allowing the platform to swing freely along the horizontal plane. There is no movement induced by the platform itself. Sway is only induced when the participant steps and shifts the center of pressure. The degree of instability and movement of the platform can be adjusted by inducing a dampening. The dampening can be set manually, either to on or off. When damping is on, the movement can be reduced by predefined percentages. The maximum displacement of the platform is thereby 100 mm to each side.

The exergames delivered by the Senso specifically target cognitive functions relevant for the successful mastering of activities of daily living, such as executive and attentional functions and physical functions such as balance and coordination. The games are played by conducting body movements, mainly steps in four directions (front, right, left, back) but also body weight shifting. An overview of the 18 existing games and the cognitive/physical domain they train is provided in Supplementary material A.

All training sessions will be supervised by a qualified study/clinic staff who will carefully observe patients while training and aid if necessary.

In general, both groups will conduct the same training program meaning it will have the same volume and the training of participants from both groups will be personalized and designed based on the same progression principles: training duration (15 min training time at the first session up to 28 min in the last session) and game difficulty (starting from rather simple and progressing to more demanding games) (26). In addition to those principles, for the intervention group the degree of instability of the labile platform also will be gradually increased (starting with 75% of the movement damped up until no dampening at the last sessions). The detailed training plan across the 4 weeks of the intervention is presented in Supplementary material B.

After each training session participants will be asked the two questions from the NASA Task Load Index (27) regarding Physical Demand and Mental Demand namely: “How mentally demanding was the training?” and “How physically demanding was the task?.” Answers at the NASA-TLX are in a scale of 1 to 20. Any answer between 10–15 is considered the “sweet spot” (20) for which the pre-defined training plan will be applied as described in Supplementary material C.

Since training intensity is decisive for the success of the intervention, in case participants rate either of the questions between 1–9 or 16–20 and in order to decrease the risk of losing the potential benefit or, respectively, the safety risk (28) the next training session will be adapted either by increasing/decreasing the duration of the next training session or by increasing/decreasing difficulty of the exergames.

Adaptations of the pre-defined plan can also be made based on the trainer’s evaluation of participant’s safety and training success, meaning they can decide at their own discretion whether the adaptation (based on participant’s perceptions) is justified or whether patients are at risk due to overestimating themselves. Figure 3 provides a detailed description of the training progression adaptation guidelines.

**Figure 3 fig3:**
[figure not shown]
Training adaptation concept.

### Outcomes

2.4

#### Primary outcomes

2.4.1

Primary outcome of this study is feasibility, defined as an umbrella term comprising several measures of acceptance and safety. They are hereinafter described.

##### Safety

2.4.1.1

Adverse events throughout the intervention period will be protocolled and categorized into serious and non-serious as well as intervention-related and intervention-unrelated. All serious intervention-related adverse events will be reported to the ethics committee.

##### Attrition

2.4.1.2

The number of participants that dropped-out during the trial will be recorded for both groups. Drop-out reasons will be documented if available. Considering the median rate for attrition in preventive interventions for older adults in community settings for clinical trials (29) a 10% attrition rate can be deemed acceptable.

##### Adherence

2.4.1.3

Attendance of each training session will be recorded in an attendance protocol by the study investigator. Average adherence rates across the intervention period will be calculated. The adherence will be calculated as the mean adherence rate (%) = number of training sessions attended / total number of training sessions offered. A review by Nyman and Victor (29) reveals a 50% attendance rate to preventive interventions for older adults in clinical trials. Nevertheless, in this study, an 80% adherence rate for the training sessions is set as the definition for being adherent to the training program.

##### Usability

2.4.1.4

The overall usability of the exergame training system will be assessed post-intervention with the System Usability Scale (SUS) (30). The SUS provides a global view of subjective assessments of usability such as the need for support, training and complexity. We use a German translation which has already been used in large studies (31). The scale was successfully applied in previous studies looking into the feasibility of exergame training in the context of inpatient rehabilitation of older adults and neurologic populations (15, 16). Based on the verbal categorization/adjective rating of Bangor (32) we expect a SUS score of at least 70 to have an “acceptable” solution (52 = ok, 73 = good, 85 = excellent, 100 = best imaginable).

##### Training load

2.4.1.5

Physical and cognitive load of each training session will be assessed using the Nasa Task Load Index (NASA-TLX). The NASA-TLX is a self-report, multidimensional assessment tool that rates perceived workload in order to assess a task, a system, or other aspects of performance (in this case the exergame training). Originally it consists of five subscales, but this study uses only: Mental Demand and Physical Demand. Answers will be in a scale of 1 to 20 (33). Answers will be presented descriptively for each training session as well as aggregated by averaging values across all training sessions (though separately for the physical and cognitive workload).

##### Enjoyment

2.4.1.6

To assess training enjoyment, we will use the Exergame Enjoyment Questionnaire (EEQ). This questionnaire consists of a 5-point Likert scale which you reflect your enjoyment and feelings from “do not agree at all” to “I fully agree” while training on the device. The score will be calculated by adding up the points of each question resulting in a minimum of 20 points and a maximum score of 100. The higher the score the greater the exergame enjoyment (34).

##### User experience

2.4.1.7

Several questions specifically tailored to this study regarding perceived safety, perceived positive effects, intention to recommend etc. will be used. Most questions will have a 7step Likert Scale answers. However, there will also be two open ended questions asking for any positive/negative feedback and other general remarks by the participants.

##### Training goals

2.4.1.8

Personal goals regarding rehabilitation/training will be assessed with the Goal Attainment Scale *(GAS)*. The GAS is an individual approach to defining and evaluating personal rehabilitation goals (35, 36). The goals will be defined at the beginning of the intervention and will be reevaluated in the middle (after 8 trainings) and at the end of the intervention period. The scale consists of a five-point rating of the achievement of the specified goals. A score of 0 corresponds to the expected improvement or achievement of the predefined goal. A negative score of −1 or −2 is considered worse than expected. A positive score of 1 and 2 is given when the goal is achieved even better than expected. Interpersonal scores for the three time-points will be evaluated descriptively for each participant separately.

The feasibility of the intervention is pre-determined using the following feasibility criteria:

no intervention-related adverse events.maximum 10% attrition rate.at least 70% adherence rate.

If all three criteria are met, we deem the intervention to be feasible. If one to two criteria are not met, the intervention is feasible but needs modifications. If none of the criteria are met, the intervention will be deemed not feasible.

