### Study design and procedures

2.1

The study is a pilot randomized control trial with two parallel groups; a control group and an intervention group with a 1:1 allocation ratio. The study will only be blinded on pre-measurement. Afterward group assignment blinding is no longer possible because the pre-assessments and training sessions will be carried out by the same study staff. Data collection will be carried out in the neurologic rehabilitation clinic in Zihlschlacht, Switzerland. All study procedures will be performed in accordance with the Declaration of Helsinki. The study protocol was reviewed and approved by the Cantonal Ethics Committee of Eastern Switzerland (EKOS 24/002). Any substantial amendment to the study protocol will have to be approved by the same Ethics Committees and the trial registration at clinicaltrials.gov NCT06296069 will be updated accordingly.

At clinic admission, patients potentially fulfilling the eligibility criteria will be informed in oral and written form about the study and asked if they wish to participate. All interested participants will then be screened for eligibility by the local principal investigator. The included participants will undergo the baseline assessments (T1) and will be subsequently randomly allocated to the intervention or the control group using permuted block randomization with blocks of four. Screening and baseline measurements will be conducted within the first two days upon admission. To minimize physical and cognitive fatigue, a consistent assessment sequence alternating between physical and cognitive tests will be enforced. Participants will be encouraged to ask for a break whenever needed. One day after the T1 measurements, the intervention period will begin. The intervention period will be equal to the length of the stay in the rehabilitation clinic (between 3–4 weeks, according to cantonal/regional regulations and insurance coverage). At the last two days before discharge, post-measurements (T2-measurements) will be performed with all (intervention & control) study participants. Participants will be withdrawn from the study if they develop symptoms or diseases regarded as exclusion criteria during the study.

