#### Statistical analyses

2.4.4

All statistical procedures will be conducted with the IBM SPSS statistics software or R (RStudio, Boston, MA, United States). For demographics as well as training adherence and compliance, all collected data will be included (i.e., including data of dropouts up to the time point of their withdrawal). For all further analyses, only data of participants with an adherence ≥70% will be analyzed (per protocol analysis). A separate descriptive analysis of data from withdrawn participants who terminated the intervention prematurely or had to be excluded during the study or participants with adherence <70% will also be provided. Data will be reported as mean (SD) values for continuous parametric data and median (IQR) values for continuous nonparametric data. Data will be tested for normal distribution using Shapiro-Wilks Test and Q-Q-plots as well as for homogeneity of variance using Levene test. General level of significance used is established as *p* = 0.05. For the physical and cognitive tests that serve as secondary outcomes and are assessed in a pre-post manner, a two-way repeated measures ANOVA with group assignment (control vs. intervention group) as between subject factor and time-point (pre- vs. post-training) as within factor will be conducted. In case length of stay (and thus number of training sessions) vary across participants, we will conduct repeat our analyses controlling for this parameter. In order to determine the effects of the outcomes, effect sizes will be calculated for all primary and secondary outcomes. If any of the assumptions for parametric testing is not met, the non-parametric alternative (Friedman’s ANOVA) will be used. If the two-way mixed ANOVA or Friedman’s ANOVA report a significant group, time or interaction effect, data will be further analyzed using post-hoc tests. To calculate effect sizes of intragroup differences between post- and baseline measurements, a dependent T-test or its non-parametric equivalent (Wilcoxon signed rank test) will be used. The effect size will be interpreted using benchmarks describing the effect size as small (r ≥ 0.01), medium (r ≥ 0.3), or large (r ≥ 0.5) (56).

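### As written, Goal Attainment Scale goals are set after allocation, when blinding has ended; the exposure is limited to GAS effect sizes and by-arm readings of GAS

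*Protocol article*

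**What the plan says.** Section 2.1 (Study design and procedures) of the protocol article fixes the order of events. "The included participants will undergo the baseline assessments (T1) and will be subsequently randomly allocated to the intervention or the control group". Then: "One day after the T1 measurements, the intervention period will begin". On blinding it says "The study will only be blinded on pre-measurement", and gives the reason: "Afterward group assignment blinding is no longer possible because the pre-assessments and training sessions will be carried out by the same study staff".

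Section 2.4.1 defines the primary outcome broadly: "Primary outcome of this study is feasibility, defined as an umbrella term comprising several measures of acceptance and safety". GAS is the eighth measure under that heading (section 2.4.1.8, Training goals). There: "The goals will be defined at the beginning of the intervention". Goals are re-rated after 8 training sessions and at the end. The scale runs from −2 to +2, with 0 for reaching the level that was expected. The same section plans a descriptive evaluation of the three time points, one participant at a time. It then gives the feasibility rule, which uses adverse events, attrition and adherence.

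Section 2.4.4 (Statistical analyses) adds a general promise: "effect sizes will be calculated for all primary and secondary outcomes".

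**The concern.** Most measures in this trial have a unit that exists independently of the staff, such as seconds, degrees or reaction time. GAS does not. Its zero point is an expectation that someone writes down for one patient. If that expectation is written when the arm is known, the arm can influence the yardstick as well as the result.

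The incentive is not far-fetched. The Introduction and the Discussion both state that training on the labile surface is expected to be more effective. Staff who share that view might write more ambitious goals for that arm; staff who worry about the unstable platform might write more modest ones. Either would change GAS scores without any difference in recovery, and no later analysis could recover a neutral yardstick. At stake is whether a GAS effect size, or a side-by-side reading of the two arms, can be taken at face value.

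**Working it through.** No formula applies, and the plan gives no figure to reproduce. The check is one of order and use.

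**Order of events (sections 2.1 and 2.4.1.8)**

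1. T1 baseline assessments, blinded.
2. Random allocation.
3. Start of the intervention, one day after T1. The staff who did the pre-assessments also deliver the training, and blinding is described as no longer possible.
4. GAS goals defined, at the start of the intervention.
5. GAS re-rated after 8 sessions, and again at the end.

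Step 4 comes after step 2. Since section 2.4.1.8 counts three time points, the first of them coincides with goal definition, so the starting score is also taken after allocation.

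**Is the start of the intervention just another name for baseline?** The article separates the two elsewhere. Section 2.4.2.2.6 (Leg proprioception) has one test done during the pre-assessment and repeated a day later, immediately before the first session. On the article's own usage, then, GAS goals sit at the later moment.

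**Who knows the arm at step 4?** Section 2.4.1.8 does not say who writes the goals. That staff and patient know the surface by then is inferred from section 2.1. The inference is a natural one, because the platform has to be set up for the first session, but it is not stated. No safeguard for goal setting is given.

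**How GAS is used**

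| Place | Use of GAS |
|---|---|
| 2.4.1.8, evaluation | Descriptive, within each participant |
| 2.4.1.8, feasibility rule | Not used |
| 2.4.4, group-by-time ANOVA | Not used; limited to the physical and cognitive tests |
| 2.4.4, effect sizes | Included by the wording, since GAS is listed under primary outcomes |

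The only route from goal setting to a reported group-level number is the last row, together with any informal comparison of the arms' GAS scores.

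**The case against.** The strongest reply is that the plan makes no between-arm comparison of GAS. Its own section describes each participant separately, the only between-arm model is reserved for secondary outcomes, and the effect-size procedure that is spelled out concerns change within a group. The sentence in section 2.4.4 is a blanket one and can hardly be meant literally for every item under the primary heading, which includes open-ended questions. The Abstract does not name GAS when it lists the components of feasibility, and no decision depends on it. This largely stands, and it sets the limit on the consequence. It does not remove the point: the blanket sentence covers GAS as worded, and per-participant scores reported from a two-arm trial invite a comparison.

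It can also be said that the timing phrase may be loose wording in a condensed article, and that personal rehabilitation goals may have nothing to do with the training surface. Both are possible. But the timing is stated, not omitted, and the text has to be judged as it reads.

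A reader might go further and infer a sizeable spurious treatment effect. For example, moving the expected level by one step in a quarter to a half of one arm's goals would move that arm's mean by 0.25 × 1 = 0.25 to 0.5 × 1 = 0.5 points, or 0.25 to 0.5 SD if the SD were 1 point. The documents do not support this as an estimate. The share, the one-step shift and the SD are all assumed, the limits at −2 and +2 are ignored, the direction could be either way, and the arm mean is not something section 2.4.1.8 plans to report.

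**Conclusion.** The point holds in a limited form. On the article's own chronology, the goals and starting score of a self-referenced measure listed under primary outcomes are fixed after allocation, when blinding has ended and with no stated safeguard. This is a risk of bias, not a demonstrated bias.

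It cannot change the feasibility verdict, and it does not touch the secondary-outcome analyses. It applies to the effect sizes promised for all primary outcomes and to any by-arm reading of GAS. Its size and direction are unknown. The conclusion rests on reading the timing phrase as written and on the inference that whoever sets the goals knows the arm. It is a cheap improvement worth making, not a flaw that threatens the trial's main conclusion.

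**What to change.** In section 2.4.1.8, change the timing of goal definition from the start of the intervention to T1, before allocation. At that visit, write down and lock the goals, all five attainment levels and the starting score. Record any later change to a goal, but score attainment against the locked version.

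The Abstract says that data collection began in February 2024, so some participants may already have goals set under the present wording. For them, report that goals were set after allocation, and do not compare GAS between arms.

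The cost is small but not nil. The goal interview moves by about one day and can use the same staff, but T1 becomes slightly longer. Screening and T1 already have to fit into the first two days, and section 2.1 takes steps against fatigue. The change helps only participants not yet enrolled and, if judged substantial, needs ethics approval under section 2.1. The mid-way and final ratings stay unblinded, so the change removes the goal-setting route to bias and leaves the rating route open.

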#### Secondary outcomes

2.4.2

Secondary outcomes of this study are measures of physical and cognitive functioning.

##### Cognitive functions

2.4.2.1

###### Cognitive flexibility

2.4.2.1.1

Cognitive flexibility will be assessed using the Trail making test (TMT): The TMT is a widely used neuropsychological test only requiring paper and pencil (37–39) and has two parts, TMT.A and TMT.B. Circled numbers from 1 to 25 are allocated randomly on a sheet which participants have to connect in the right order (TMT.A). At TMT.B, circled numbers and letters are randomly allocated on a sheet and the participants have to connect circled numbers and letters in the right order and in alternating manner. The required time to complete each task as well as the difference between the scores TMT.B-TMT.A measured in both parts will be evaluated.

###### Psychomotor speed

2.4.2.1.2

The *Step Reaction Time Test* will be conducted using the Dividat Senso and it measures psychomotor speed in terms of reaction to visual stimuli using the lower extremities in 6 directions (front right, front left, right, left, back right & back left). There are six light grey triangles on the screen and each time one of then turns black, participants need to step as quickly as possible in the respective direction (Figure 4). Average reaction time across all stimuli will be used for analyses.

